#### 2.4.2. Application Development

Simultaneously, the same working group that designed the intervention designed the application describing the characteristics of an app meant both to store activity and sleep data and able to send motivational messages to the user whenever an activity decline or sleep problem was identified. The group designed the algorithms thought to classify adherence or lack of it regarding physiotherapist prescriptions. After putting the software development out to tender—a must, as the project is receiving public funding—the selected app developer software company (Mass Factory Urban Accessible Mobility S.L., Barcelona, Spain) was contacted and the team started a co-creative process including several software engineers and designers to create an ad-hoc-made app both to register and store the participants’ physical activity, exercise compliance and sleep patterns and to send the already mentioned motivational messages when needed.

The result of this process was a user-friendly smartphone application—IDEApp—that can be synchronised to a smart band. The smart band will register, store data regarding physical activity (i.e., heart rate) and sleep patterns, as well as provide information about daily exercise practice. IDEApp will collect two types of data: objective and self-informed. Objective data will include the number of daily steps, aerobic exercise—including minutes, distance in metres, and maximum, minimum and average heart rate—and sleep structure, including duration in a 24-h period, and deep and light sleep discrimination. On the other hand, self-reported data will require participants to simply indicate on IDEApp whether they have performed one of three exercise options: (1) relaxation, (2) stretching, or (3) strength and endurance.

When non-compliance with the exercise prescription, physical activity decreases, or altered sleep patterns are detected, the system will trigger motivational or awareness messages through the app. The motivational messages were classified according to 12 potential situations following an algorithm based on the percentage of exercise prescription performed and the number of hours of sleep. A pool of more than 50 motivational messages was created for each category. Detailed information about the algorithm and type of messages is displayed in Table S3 presented in Supplementary Material. Accessibility options of IDEApp include features relating to language (Spanish or Catalan) and text size. Screenshots of IDEApp running can be found in Figure 2. Messages’ function will be “on” for only one of the trial arms and “off” for the rest of subjects. The app was named “IDEApp” for obvious reasons.

#### 2.4.3. Criteria for Discontinuing or Modifying Allocated Interventions

Participants may withdraw from the study for any reason at any time. The investigators also may withdraw participants from the study in order to protect their safety and/or if they are unwilling or unable to comply with required study procedures (i.e., health care providers notice a serious adverse event including hypomania or mixed features).

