### 2.3. Eligibility Criteria

All participants will meet the following inclusion criteria: aged 18–65 years, presenting mild to moderate depressive symptoms according to the Montgomery–Asberg Depression Rating Scale (MADRS score > 16 and <34), currently owning an Android-compatible smartphone, fluent in Spanish language, basic knowledge and skills using a smartphone, and able to provide written informed consent to participate. Potential participants will be excluded as per the following exclusion criteria: severe cognitive and/or physical impairment; cognitive deficit or developmental disorder; current psychotic, melancholic or catatonic futures; drug or alcohol dependence; modification of drug treatment (or its dose) in the last month; beginning of psychological treatment in the last month; beginning of biophysical treatment in the last month; BMI > 40; physical disability. Any general practitioner, nurse, psychologist or psychiatrist treating the patient will make the referral.

Group sessions will be facilitated by a psychologist ([name]) and a physiotherapist ([name]) with accredited experience who will receive a brief therapy training.

Before any study procedures occur, participants will be informed about the study characteristics, they will be provided with a study information leaflet and a written informed consent form must be signed by them. After signing the informed consent, an experienced (more than five years of regular clinical practise since specialisation) clinical psychologist or a psychiatrist will confirm or disregard depressive symptomatology, administer the MADRS and judge that the subjects fulfil all the inclusion criteria items and none of the exclusion criteria requirements.

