### 2.12. Data Collection and Management

#### 2.12.1. Plans for Assessment and Collection of Outcomes

A trained psychologist ([name]) and a physiotherapist ([name]) will carry out the assessments. Evaluation instruments have been described in the Outcomes section, and time points and assessment tools are outlined in Table 2.

Following referral, participants will attend the study entry clinical interview and baseline assessment, followed by an evaluation with a physiotherapist to identify their physical needs and capabilities. Such assessments will allow for the subsequent prescription of tailored exercise to the intervention groups. After baseline assessment, the study staff will install IDEApp on the smartphone of all participants and provide them with the smart band. Instructions on how to use both will be provided, alongside written information with basic information and contact information (e.g., help phone or email) where technical issues regarding device use will be resolved. In the first week after study entry, all subjects will effectively start using the devices and IDEApp, which will provide estimates of their baseline physical activity and exercise, and up until the end of the trial by implementing ecological momentary assessment methods (EMA). This monitoring system using a wearable band and a mobile phone-based EMA includes objective measures of physical activity and health variables, such as heart rate, walking and sleep patterns, and is intended to be minimally invasive to the users and their mobile phone usage. The EMA methods are expected to provide with accurate data on activity changes that will allow for adapting motivational messages according to the activity states.

After completion of the group sessions (or after 1 month for Control Group), every participant will be followed-up for eight months. Post-allocation assessments following the intervention at 4 weeks (T1) and 12 weeks (T2) will be carried out by telephone in order to ease the burden of participants. These assessments will last 30 min and will be performed from the facilities of the Centre Fòrum in order to guarantee data safety. The final assessment at 36 weeks (T3) will be carried out face-to-face and will follow a similar outline as the baseline assessment, and again will be carried out by a psychologist and a physiotherapist.

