## 3. Statistical Methods

### 3.1. Statistical Methods for Primary and Secondary Outcomes

Statistical analysis will be performed using the software SPSS Statistics 25 (IBM Corp., Armonk, NY, USA). Descriptive statistics will be used to analyse the distribution of socio-demographic and clinical characteristics among groups at baseline. Continuous variables with a normal distribution will be analysed performing an ANOVA. Where the premises of normalcy are not met, the Wilcoxon test will be used. The differences between groups on the categorical and mail clinical variables will be evaluated by using a Chi-square test. Those variables that are statistically significant may be used as covariates for a logistic or linear regression study of the factors associated with the magnitude of the effect, and determine which variables are better predictors of functioning. The effect size index will be estimated in case of correlation indexes for each of the performed analyses. To analyse efficacy, we will perform intention to treat analysis. Analysis will be two-tailed and the significance set a *p* < 0.05.

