### 3.2. Methods in Analysis to Handle Protocol Non-Adherence and Any Statistical Methods to Handle Missing Data

Last Observation Carried Forward analysis will be used to handle and minimise missing data on the clinical variables.

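### Section 2.4.3 gives investigators only discretionary withdrawal from the study, with no option to stop or modify the intervention while outcome assessment continues

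*Protocol article*

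**What the plan says.** All references are to the protocol article.

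- **2.4.3** is titled as criteria for discontinuing or modifying the allocated interventions. Its text covers only leaving the study. Participants may leave for any reason. As for investigators: "The investigators also may withdraw participants from the study in order to protect their safety". A second ground is that participants are "unwilling or unable to comply with required study procedures". The example given is that "health care providers notice a serious adverse event including hypomania or mixed features".
- **2.11 (Blinding)** says that if a risk situation is detected, the blind is broken, the clinician is told, and ending participation is discussed according to circumstances.
- **2.12.1** says that "every participant will be followed-up for eight months". The week 4 and week 12 assessments "will be carried out by telephone in order to ease the burden of participants" and last 30 minutes. Week 36 is face to face.
- **3.1**: "To analyse efficacy, we will perform intention to treat analysis".
- **3.2**, whose heading covers both non-adherence and missing data, gives one method: "Last Observation Carried Forward analysis will be used to handle and minimise missing data on the clinical variables".
- **2.5.1** and **Table 2** make the SF-36 the primary outcome, measured at baseline and at 4, 12 and 36 weeks.

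**The concern.** Stopping treatment and leaving the trial are different events. A participant who becomes hypomanic may need to stop exercising, or to stop receiving messages. That person seldom needs to stop answering a questionnaire by telephone. Section 2.4.3 promises rules on the first kind of event and supplies only the second.

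When the rule is used as written, the primary outcome would be missing because of something that happened after randomisation and because the investigator chose to end participation. LOCF then carries forward a score that may predate the event. If functioning later falls, the primary outcome does not show it. If the person recovers and benefits, that is hidden too. Unlike ordinary drop-out, this loss comes from the protocol's own wording and could be avoided. A better missing-data method would not cure it, because the values would still not have been collected.

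**Working it through.** **1. Is there any other route in the text?**

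| Section | What it offers after a safety event or non-compliance |
|---|---|
| 2.4.3 | Withdrawal from the study, at the investigator's discretion |
| 2.11 | Unblinding, informing the clinician, discussion of ending participation |
| 2.12.2 (retention) | Reminders, contact when band records are missing, flexible visits; nothing on participants who stop the intervention |
| 3.2 | LOCF |

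None of these stops or modifies the intervention while stating that assessment continues.

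**2. How many SF-36 values are at risk per person?** There are three post-baseline assessments (Table 2).

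- Withdrawal before week 4: 3 of 3 left to LOCF.
- Between weeks 4 and 12: 2 of 3.
- Between weeks 12 and 36: 1 of 3.

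**3. What could this do to the primary contrast?** The plan gives no rate of investigator withdrawal, so there is no figure to reproduce and what follows is illustration.

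Inputs from the plan: A + B = 48 + 48 = 96, Control = 76 (2.1); primary comparison A + B against Control (2.5.1); planned effect d = 0.5 and 20% drop-out (2.6).

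Assumed: *w* is the share of an arm withdrawn by the investigator. *u* is the true later value minus the carried-forward value, in SD. Week 36 is taken as the time point, because 2.5.1 names none.

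Error in contrast = −(*w*_I × *u*_I − *w*_C × *u*_C), where I is A + B and C is Control.

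*(a) Events in A + B only.* This is a bounding case, not a claim that events fall there. With *k* people, *w*_I = *k*/96 and *w*_C = 0.

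| *k* | *u* = +0.5 | *u* = −0.5 | *u* = −1.0 |
|---|---|---|---|
| 1 | −0.5/96 = −0.005 | +0.005 | +1.0/96 = +0.010 |
| 5 | −2.5/96 = −0.026 | +0.026 | +5.0/96 = +0.052 |

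Against d = 0.5, these are 1.0% to 5.2% for *u* = ±0.5 and 2.1% to 10.4% for *u* = −1.0. A negative sign understates the benefit of the programme; a positive sign overstates it.

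*(b) Same share withdrawn in both comparison groups.* The error becomes −*w*(*u*_I − *u*_C). If the unseen courses are alike it is zero. With *w* = 5% and courses differing by 0.5 SD, it is 0.05 × 0.5 = 0.025 SD in size.

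*(c) Ceiling.* If the whole planned 20% loss were of this kind, in A + B only, with *u* = +0.5, the shift would be 0.20 × 0.5 = 0.10 SD. The apparent effect would be 0.40, and power at 96 against 76 would fall from 0.90 to 0.74. Nothing in the plan suggests that investigator withdrawals would approach this.

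**The case against.** Several points on the other side are sound.

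- **Withdrawal is discretionary.** Section 2.4.3 says investigators *may* withdraw someone, and 2.11 describes a case-by-case response. A reader might infer that every safety event ends data collection; the text does not support that. It remains true that leaving the study is the only outcome either section mentions.
- **The loss of SF-36 values is inferred.** No sentence says that assessments stop, and 2.12.1 could be read as continued follow-up for everyone. A condensed article may also leave the detail to a fuller document. However, the article is not silent: it has a section for this purpose and fills it with withdrawal from the study, whose ordinary meaning is that assessment ends.
- **Non-compliance concerns study procedures, not exercise.** A reader might infer that participants who do not exercise would be removed. The documents do not say so. Poor adherence triggers messages in Intervention A, and missing band records prompt contact in all arms. If the procedures refused are the assessments themselves, the SF-36 is missing whatever 2.4.3 says. But the term is undefined and could be applied to group sessions or band use.
- **Intention to treat is not contradicted outright.** Analysing everyone as randomised with carried-forward values is consistent with 3.1 and 3.2. The fit is poor because the rule allows outcomes to go uncollected for reasons arising after randomisation.
- **LOCF is the larger issue.** It applies to every drop-out. This point covers only the part of the missing data that the protocol itself would create.

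**Conclusion.** The point holds as a minor defect of design wording. The rule in 2.4.3 does not match its heading, no other section repairs it, and using it as written would create avoidable gaps in the primary outcome.

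The effect is probably small. With 1 to 5 intervention participants affected and none in control, it is 0.005 to 0.026 SD for an unseen change of 0.5 SD in either direction, and up to 0.052 SD for a fall of 1.0 SD. These figures rest on assumed counts, assumed courses, carry-forward of a single earlier value, and week 36 as the time point. Similar events and courses in the two comparison groups would cancel some or all of the shift. The sign cannot be predicted, and the documents support no claim of imbalance between arms.

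A reader might also infer that hypomania or mixed features should join "current psychotic, melancholic or catatonic futures" among the exclusions in 2.3. The point does not support that: it would narrow a deliberately symptom-based sample and would not keep anyone in follow-up.

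**What to change.** Reword 2.4.3 along these lines:

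1. For a safety event in any arm, the investigator may stop or modify the relevant components: group sessions, exercise prescription, motivational messages, or band and app use. Controls have only the band and app, so the wording must cover those.
2. Non-compliance with any intervention component is not a ground for withdrawal from the study.
3. In both cases the 4-, 12- and 36-week assessments continue unless the participant withdraws consent to follow-up or an assessment is itself unsafe (for example, a physical test at week 36, in which case the questionnaires can still be taken).

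Align the sentence in 2.11 on ending participation with this, so that it separates stopping the intervention from leaving follow-up. Leave the eligibility criteria in 2.3 as they are.

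The cost is protocol wording. Two 30-minute telephone assessments and one visit per participant are already planned, so the extra work is close to nil.

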#### 2.4.4. Strategies to Improve Adherence to Interventions

The inclusion of a mobile support tool (IDEApp) that delivers motivational messages and a smart band in the trial is not a core part of the intervention but, rather, a way to monitor activity and sleep patterns, and a strategy to improve adherence to the intervention, which has the potential to prolong motivation and exercise performance in the long term. All participants will benefit from monitoring their exercise physical activity and sleep patterns, regardless of their allocation to study condition. In addition, IDEApp will deliver motivational messages to participants allocated to Intervention A when the smart band detects activity decrease, non-compliance with the exercise prescription or strange sleep patterns.

#### 2.4.5. Relevant Concomitant Care Permitted or Prohibited during the Trial

This study seeks to investigate the effects of personalised exercise in addition to standard of care. It tests a trans-paradigmatic intervention that does not require therapist—or user—to strongly adhere to—or renounce—ideological models of mental health. It is fully compatible with other psychological therapies. All concomitant care and interventions are permitted if they were implemented more than a month before study entry.

### 2.5. Outcomes

#### 2.5.1. Primary Outcome Measure

Given the great heterogeneity expected in the sample of patients, the intervention is aimed at improving global functioning in the first place. The functional impairment will be assessed using the 36-item Short-Form Health Survey (SF-36v2, Quality Metric Inc., Lincoln, NE, USA) [13,14]. As the main target of the trial is to learn about the efficacy of personalised exercise prescription, the main outcome comparison will be (Intervention A + Intervention B) vs. Control, being the comparison of A vs. B vs. C considered as secondary.

#### 2.5.2. Secondary Outcome Measures

All the Secondary outcomes will compare both (A + B) vs. C and A vs. B vs. C.
Depressive symptoms using the Patient Health Questionnaire (PHQ-9) [15,16].Well-being measured by the World Health Organization Well-Being Index (WHO-5 WBI) [17,18].Motivation for exercise using the Spanish validation of the Exercise Motivations Inventory (EMI-2) [19,20].To identify their physical needs and capabilities, we will measure:Current physical activity using the Simple Physical Activity Questionnaire (SIMPAQ) [21].Functional exercise capacity using the 6 min walking test (6MWT) [22]. The change in the distance walked in the 6MWT after completion of the programme will be used to trace the natural history of change in exercise capacity over time. Before the test, a finger pulse oximeter will be attached to participants to record baseline and final heart rate and oxygen saturation. For the evaluation of perceived exertion, the short Borg CR 10 Scale [23] will be used before and after the test. This modified Borg scale has a score range from 0 to 10 and seems more appropriate than the longer Borg 15 Graded Category Scale, which requires a greater differentiation capacity. The Borg CR 10 Scale showed moderate reliability for patients with depressive and anxiety disorders [24].Functional exercise capacities using the 1 min sit-to-stand test [25].Isometric muscle strength of the hand and the forearm using the handgrip strength test [26]. The equipment used will be a digital hand dynamometer (JAMAR^®^, Nottinghamshire, UK) [27], and grip strength will be measured 3 times per hand in the 2-handle position.

For all the questionnaires, we will be using the validated versions in the Spanish language.

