### 2.4. Interventions

#### 2.4.1. Intervention Description

The main goal of the intervention is to personalise exercise prescription and enhance motivation towards being physically active. To fulfil our objectives, a collaborative team of 4 psychologists, 2 Physical Medicine and Rehabilitation specialists (one medical doctor specialised in the field and one physiotherapist), and 1 psychiatrist designed a brief group intervention—the IDEA programme.

The programme will consist of six 90 min group sessions composed of four to six participants as working with small groups facilitates the patient’s integration and allows professionals to better detect their needs. These short intervention sessions will be distributed in one month, with a frequency of once or twice a week depending on the week of the programme. Group sessions will take place in the therapy room of Centre Fòrum–Parc de Salut Mar, which provides rehabilitation, sociosanitary and mental health services. In the exercise-oriented sessions, participants will be asked to wear sports clothes to practise the individualised exercise prescription on-site and will receive an individual brochure with indications and photographs of their prescription.

For the implementation of the sessions, we created a guide for the professionals where the content of each session and its dynamics were outlined. In the case of the individualised exercise prescription, a pool of exercises was created in order to standardise the potential exercises that will be chosen individually for each participant. Table 1 presents an overview of the IDEA programme. Detailed information regarding the content of the group sessions is available in Table S1 as Supplementary Material.

The exercise prescription will be personalised in terms of intensity and amount of time. Therefore, all participants will perform four types of exercise: stretching, aerobic, strength and relaxation. We have designed three types of programmes covering low, moderate and high intensity. Participants with higher levels of sedentarism will be prescribed 45 min sessions twice a week, while participants with lower levels will do 60 min sessions three times a week.

Participants will choose the type of aerobic exercise according to their preferences and possibilities (i.e., having easy access and knowing how to perform the exercise). Options can include—but are not limited to—walking, running, water aerobics, biking or dancing.

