**Figure 2 ijerph-18-06306-f002:**
[figure not shown]
Screenshots of IDEApp running on a smartphone (messages in Catalan). (**A**)—login and register screen; (**B**)—home Screen without notification; (**C**)—home screen with motivational notification.

**Table 1 ijerph-18-06306-t001:** Description of the content of the IDEA group sessions.

Session
1 Depression and exercise
2 Motivation towards exercise
3 Introduction to the exercise prescription
4 Barriers to exercise
5 Review of the exercise on prescription
6 What now? Exercise maintenance

**Table 2 ijerph-18-06306-t002:** SPIRIT diagram of the IDEA trial.

	Study Period					
	Enrolment	Allocation	Post-Allocation			Close-Out
Time point	−*t*_1_	*t* _0_	4 Week group sessions	*t* _1_	*t* _2_	*t* _3_
Enrolment:						
Eligibility screen	X					
Informed consent	X					
Allocation		X				
Interventions:						
Intervention A			X	X	X	X
Intervention B			X	X	X	X
Control group				X	X	X
Assessments:						
Sociodemographic data		X				
Health habits and clinical data		X				
SF-36		X		X	X	X
WHO-5 WBI		X		X	X	X
PHQ-9		X		X	X	X
SIMPAQ		X		X	X	X
6 min walking test		X				X
1 min STS test		X				X
Hand grip strength test		X				X
EMI-2		X				
Activity and sleep monitoring		X	X	X	X	X
Delivery of motivational messages				X	X	X

SPIRIT = Standard Protocol items: Recommendations for Interventional Trials [29].; *t*_1_ = pre-allocation; *t*_0_ = baseline assessment; *t*_1_ = post-allocation assessment at 4 weeks; *t*_2_ = post-allocation assessment at 12 weeks; *t*_3_ = final assessment at 36 weeks; SF-36 = 36-item short-form health survey; WHO-5 WBI = world health organization well-being index; PHQ-9 = patient health questionnaire; SIMPAQ = simple physical activity questionnaire; STS = sit-to-stand; EMI-2 = exercise motivations inventory.

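### Exercise motivation (EMI-2) is a secondary outcome to be compared between arms, but the schedule measures it only at baseline

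*Protocol article*

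**What the plan says.** Section 2.5.2 (Secondary Outcome Measures) opens with a rule for the whole list: "All the Secondary outcomes will compare both (A + B) vs. C and A vs. B vs. C". One item on that list is "Motivation for exercise using the Spanish validation of the Exercise Motivations Inventory (EMI-2"). Nothing exempts it from the rule.

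Section 2.12.1 refers the reader elsewhere for the timing of measurements: "time points and assessment tools are outlined in Table 2". In Table 2 the EMI-2 row has a single mark, in the allocation column (t0), which the table's footnote defines as the baseline assessment. Its cells for the group-session period, t1 (4 weeks), t2 (12 weeks) and t3 (36 weeks) are empty.

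Section 2.4.1 gives the purpose of the intervention: "The main goal of the intervention is to personalise exercise prescription and enhance motivation towards being physically active".

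**The concern.** The outcome list promises a between-arm comparison of motivation, but the schedule does not collect the data for one. With only a baseline value there is no change score and no post-treatment contrast. What remains is a comparison of the arms before treatment. A significant result there would come from chance or from a problem in allocation, yet it would be reported under the heading of a secondary outcome.

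Motivation also matters to the trial's question. Raising it is part of the stated main goal in section 2.4.1, one of the six group sessions is devoted to it (Table 1), and arms A and B differ only in the app's motivational messages (section 2.1). EMI-2 is the only listed outcome that measures exercise motivation directly. As scheduled, the trial could not say whether motivation changed in any arm. Follow-up values that are not collected cannot be recovered at the analysis stage.

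**Working it through.** There is no figure in the plan to reproduce. The check sets the outcome list in section 2.5.2 against the marks in Table 2.

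**1. Marks per outcome in Table 2**

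| Outcome | Role | t0 | t1 | t2 | t3 | Post-baseline marks |
|---|---|---|---|---|---|---|
| SF-36 | primary | X | X | X | X | 3 |
| PHQ-9 | secondary | X | X | X | X | 3 |
| WHO-5 | secondary | X | X | X | X | 3 |
| SIMPAQ | secondary | X | X | X | X | 3 |
| 6 min walk | secondary | X | – | – | X | 1 |
| 1 min sit-to-stand | secondary | X | – | – | X | 1 |
| Hand grip | secondary | X | – | – | X | 1 |
| **EMI-2** | **secondary** | **X** | **–** | **–** | **–** | **0** |

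Six of the seven secondary outcomes have at least one post-baseline mark. EMI-2 is the exception, with 0 of 3.

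**2. Is this an artefact of reading the table?** Probably not. The EMI-2 row splits into seven cells, which matches the label column plus six period columns, and the mark falls in the t0 column. The physical-test rows just above it kept their second mark (for example "6 min walking test X X"), so the table does show repeats at the final visit where they are planned.

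**3. Does t0 precede treatment?** Yes. Section 2.1 places the group sessions after baseline assessment, and the messages start in week 4. No t0 value can contain an effect of either.

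**4. What can be estimated?** Write Y0 for EMI-2 at baseline and Yk for its value at follow-up visit k.

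- Change, Yk − Y0: undefined for k = 1, 2, 3, because no Yk is collected.
- Post-treatment contrast, mean Yk in A + B minus mean Yk in control: undefined for the same reason. The three-arm comparison is undefined too.
- Baseline contrast, mean Y0 in A + B minus mean Y0 in control: computable, but its expected value under sound allocation is zero whatever the treatment does.

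**5. Does the missing-data rule help?** No. Section 3.2 specifies last observation carried forward. Applied here it sets Yk = Y0 for every participant, so Yk − Y0 = 0 in all arms, and the contrast at visit k is the baseline contrast again.

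**The case against.** The strongest reply is that the defect may lie in Table 2 and not in the design. Section 2.12.1 says the 36-week visit "will follow a similar outline as the baseline assessment", and EMI-2 is given at baseline, so a mark at t3 may simply have been left out. That is possible. However, the wording is general and does not name EMI-2, and the same section defers to Table 2 for time points. If a 36-week measurement was intended, the table is wrong and still has to be corrected.

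The opposite reading is also open: EMI-2 may be a baseline descriptor placed under the wrong heading. The abstract's list of data collected over follow-up leaves out motivation, which agrees with Table 2. This is weak evidence, because the same sentence puts exercise capacity at 4 and 12 weeks, where Table 2 has none. On this reading section 2.5.2 is what needs correcting.

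On importance, the trial's main objective is functioning, the primary outcome is SF-36, and section 2.4.4 describes the app and messages as an adherence aid and not as a core component. No other comparison depends on EMI-2, and SIMPAQ and the smart band follow behaviour over time. All of this stands and limits the severity. Activity data do not measure motivation itself, however.

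The article's brevity is no answer. Outcome status and schedule are both stated, and they conflict. An analysis plan cannot analyse values that the visits do not collect.

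**Conclusion.** The concern holds. Followed as written, the plan compares the arms on a secondary outcome with no post-baseline measurement (0 of 3 visits), so both planned EMI-2 contrasts are uninterpretable as treatment effects. The conclusion rests on Table 2 being the operative schedule, as section 2.12.1 says it is. If the table has an omission, the contradiction remains and the error moves to the table. The effect is confined to one of seven secondary outcomes. The primary comparison and the sample size are untouched. It should be corrected because the measure bears directly on part of the intervention's stated goal and the missing follow-up values could not be obtained later.

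**What to change.** Reconcile section 2.5.2 with Table 2 in one of two ways.

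- **Keep EMI-2 as an outcome.** Administer it at the 36-week visit, which is already face-to-face and modelled on the baseline visit, and add the mark at t3 in Table 2. A further measurement at 4 weeks, when the group sessions end, would be useful but is optional. It would have to fit a 30-minute telephone call that was chosen to limit participant burden.
- **Drop it as an outcome.** Remove EMI-2 from the list in section 2.5.2 and describe it as a baseline characteristic. If it is wanted as an effect modifier, that use should be prespecified.

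The first option costs one questionnaire at an existing visit. The second costs one deleted line and gives up any direct evidence on whether motivation changed. If EMI-2 was always meant to be given at 36 weeks, only the table needs correcting.
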